### 2.6. Sample size (14)

The sample size calculation is based on the results of previous studies. The incidence of aspiration pneumonia in previous studies was 0.091 (4/44) in the intervention group and 0.292 (14/48) in the control group.^[17]^ The sample size has been calculated with a 2-tailed significance level of 5% and a power of 80%, resulting in 118 participants (59 in each group). To account for 20 dropouts, the calculation 118 + 20 = 138 suggests that 138 patients should be recruited. This value has been rounded off to 140 patients.

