### 2.11. Statistical methods (20a, 20b, 20c)

#### 2.11.1. Statistical methods for primary and secondary outcomes (20a).

Statisticians will independently undertake statistical analyses. Parametric data will be presented as mean ± standard deviation, whereas non-parametric data as median and 95% confidence interval. Two-tailed *t* tests and chi-squared tests will be used to compare the demographic and clinical characteristics of the 2 groups at baseline. MMSE, BI, and total caloric intake at baseline and endpoint will be compared between the 2 groups using repeated-measures analysis of variance. The number of febrile days in the 2 groups was compared using the 2-tailed *t* test. The probabilities of being pneumonia-free and survival from pneumonia-related deaths will be estimated using the Kaplan–Meier product-limit method. Pneumonia-free survival rates will be calculated from the date of random assignment to the date of pneumonia onset, date of death, or cutoff date for patients alive at the time of closure of the dataset. A Cox proportional hazards regression model will be used to examine the relationship between modifiable factors and the incidence of pneumonia or pneumonia-related mortality. Relative risks) and 95% confidence interval will be calculated from 2-by-2 tables. Plausible predictors (age, sex, ease of diagnosis, duration of illness, activities of daily living, cognitive function, and treatment assignment) will be included in the original model. Backward stepwise regression will be performed, and *P* > .2 will be used for variable removal. Statistical analysis will be performed using SPSS software (version 21.0; IBM, Armonk, NY). All statistical tests will be 2-sided, and the statistical significance threshold will be set at 5%.

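### Treatment assignment can be removed by stepwise selection from the only regression model for pneumonia, so the adjusted hazard ratio may be missing or, if the true effect is smaller than planned, exaggerated

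*Protocol article*

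**What the plan says.** Section 2.11.1 of the protocol article describes one regression model for pneumonia: "A Cox proportional hazards regression model will be used to examine the relationship between modifiable factors and the incidence of pneumonia", or pneumonia-related mortality. The predictors are age, sex, ease of diagnosis, duration of illness, activities of daily living, cognitive function and treatment assignment. The text continues: "cognitive function, and treatment assignment) will be included in the original model. Backward stepwise regression will be performed". The selection rule in full is: "Backward stepwise regression will be performed, and *P* > .2 will be used for variable removal". No sentence keeps treatment in the model.

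The same section plans two other summaries of pneumonia. Relative risks with a "95% confidence interval will be calculated from 2-by-2 tables", without naming the row variable. The probability of being pneumonia-free "will be estimated using the Kaplan–Meier product-limit method", with no between-group test named. Treatment assignment is explicitly linked to pneumonia only in the Cox model.

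Section 2.6 sizes the trial on two proportions, 0.091 (4/44) against 0.292 (14/48), at two-sided 5% and 80% power, "resulting in 118 participants (59 in each group".

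**The concern.** In a randomised trial the treatment term is the contrast the design exists to estimate, so whether it is reported should not depend on its p-value. Under the stated rule it is treated like any other candidate.

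Two things follow. If treatment's p-value exceeds .2 when it is considered for removal, the adjusted hazard ratio and its interval disappear. If treatment survives, it does so because the estimate was far enough from 1. The reported ratio is then conditional on that, and the usual 95% interval makes no allowance for it. The adjusting covariates also become data-dependent, chosen from a list that is long for the number of events expected.

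**Working it through.** **Inputs.** From section 2.6: risks 0.091 and 0.292, 59 per group, two-sided 5%, 80% power. From section 2.11.1: seven candidates, removal at P > .2. True hazard ratios (HRs) other than the planned one, and all covariate effects, are assumptions; the article gives none.

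**1. The plan's own figure.** Pooled-variance formula for two proportions, no continuity correction:

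n = [1.960·√(2·0.1915·0.8085) + 0.8416·√(0.091·0.909 + 0.292·0.708)]² / 0.201² = (1.0907 + 0.4528)² / 0.0404 ≈ 59 per group.

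The stated sample size is reproduced.

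**2. Events and planned HR.** Expected events: 59 × (0.091 + 0.292) = 22.6. Per candidate: 22.6 / 7 = 3.2. Under proportional hazards over 12 months, HR = ln(1 − 0.091) / ln(1 − 0.292) = 0.276. The event count is for pneumonia alone; an endpoint that adds deaths would have more.

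**3. Chance that treatment is removed.** Two-sided P > .2 means |Z| < 1.2816. With information of events/4, Z has mean −θ, where θ = |ln HR|·√(events/4). So

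P(removed) = Φ(1.2816 − θ) − Φ(−1.2816 − θ).

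For each HR, the treated-arm risk is 1 − (1 − 0.292)^HR. Worked example at HR 0.6: risk 0.187, events 59 × (0.187 + 0.292) ≈ 28.2, θ = 0.511 × √(28.2/4) ≈ 1.36, P = Φ(−0.08) − Φ(−2.64) ≈ 0.47.

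The simulation column comes from backward elimination in a seven-variable Cox model (59 per group, 12 months, 1,000 runs per scenario, log HR of 0.3 assumed for three covariates and 0 for the other three).

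| True HR | Events | Removed, formula | Removed, simulation |
|---|---|---|---|
| 0.276 (planned) | 22.6 | 3.8% | 5.1% |
| 0.5 (assumed) | 26.6 | 31% | 30% |
| 0.6 (assumed) | 28.2 | 47% | not run |
| 0.7 (assumed) | 29.9 | 61% | 58% |
| 1.0 (assumed) | 34.4 | 80% | 79% |

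A separate simulation with 120 patients gave 7%, 34%, 47% and 80% at HRs of 0.28, 0.5, 0.6 and 1.0. Its covariate effects are not recorded, so it is only a rough check. If all 140 recruits were analysed (70 per group), the formula gives 2%, 25%, 58% and 80% at HRs of 0.276, 0.5, 0.7 and 1.0.

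**4. Exaggeration when treatment is retained.** Median estimated HR in the first simulation:

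| True HR | Treatment forced in (full model) | Only when retained by selection |
|---|---|---|
| 0.276 | 0.257 | 0.256 |
| 0.5 | 0.473 | 0.397 |
| 0.7 | 0.679 | 0.501 |
| 1.0 | 1.002 | 0.532 (retained estimates below 1) |

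The reason is visible in the cut-off. At a true HR of 0.6 the standard error of the log HR is 2/√28.2 ≈ 0.377, so a beneficial estimate survives only if it is below exp(−1.2816 × 0.377) ≈ 0.62. Nearly every surviving beneficial estimate is then better than the truth. At the planned effect the cut-off hardly matters. The full model drifts slightly from the truth (0.473 for 0.5), so a small part of the retained shift is not due to selection.

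**The case against.** The strongest reply is that the Cox model is not the trial's main treatment comparison. Its stated aim is to relate modifiable factors to pneumonia, which reads as a risk-factor analysis, and nothing labels its hazard ratio as the primary estimate. The sample size rests on two proportions, which fits a 2-by-2 comparison. This stands in part. A reader might infer that the trial could end with no treatment estimate for pneumonia. The article does not support that: it also plans relative risks with confidence intervals and Kaplan–Meier estimates. Although neither is said to be by treatment group, an unadjusted estimate would probably still be reported.

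The reply does not rescue the selection rule. Treatment is named among the removable terms, age and sex in the same list are not modifiable factors, and no other regression for pneumonia is planned.

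The other objections also narrow the point:
- At the only effect the article supports, removal is rare and exaggeration negligible. The larger figures depend on assumed hazard ratios.
- A treatment term dropped at P > .2 was not near significance at 5% when dropped. The loss is of an estimate and its interval, not of a positive result.
- The Cox model is not the only model of any treatment effect. MMSE, Barthel index and caloric intake are compared between groups by repeated-measures analysis of variance.
- A reader might infer that ease of diagnosis is not collected, or that it concerns how the outcome is detected. Neither is established: section 2.9 gives an open list, Figure 3 is not shown, and the term is not defined.

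**Conclusion.** The point holds for the adjusted hazard ratio. As written, the rule that P > .2 "will be used for variable removal" applies to treatment assignment in the only regression model for pneumonia. The adjusted treatment HR may therefore be missing. If the true effect is smaller than planned, a reported HR will tend to be exaggerated, with an interval that ignores the selection.

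The risk of removal is about 4–5% at the planned HR of about 0.28. Under assumed true HRs it is about 31% at 0.5, 47% at 0.6 and 80% at 1.0. These figures assume 59 per group, the planned control risk of 0.292, proportional hazards and 12 months of follow-up. The smaller effects deserve attention because the planned one comes from groups of only 44 and 48 patients.

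**What to change.** In section 2.11.1:
- Force treatment assignment into the Cox model, with a small prespecified set of baseline covariates already collected, for example age, Barthel index and MMSE. The exact choice is the investigators'.
- Report the treatment HR and its 95% CI whatever the p-value.
- Confine stepwise selection to a separately labelled exploratory risk-factor analysis, with treatment always retained.
- Define ease of diagnosis as a baseline variable, or drop it.

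This takes a few sentences, needs no new data and leaves the sample size unchanged. It should be settled before the database is locked and treatment assignments are revealed.

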### 2.12. Data monitoring

#### 2.12.1. Composition of the data monitoring committee, its role and reporting structure (21a). 2.12.

The principal investigator will ask the data controller and monitoring personnel to monitor the study to ensure that it is being conducted safely and in accordance with the research protocol with accurate data collection.

The principal investigator will prepare a monitoring plan, and the data controller and monitoring staff will conduct monitoring in accordance with the monitoring plan.

### 2.13. Harms

#### 2.13.1. Adverse event reporting and harms (22).

Adverse events, such as signs, symptoms, and other discomfort, will be observed and recorded in detail during the study. The attending physician will take appropriate action in the event of a serious adverse event or failure and report it to the principal investigator of the institution. The principal investigator will review information regarding the type of adverse event, the severity classification, the severity and reason for the determination of severity, predictability, the causal relationship with the intervention, the history of the event, and the participant identification. Severity classification will be determined according to the National Cancer Institute Common Terminology Criteria for Adverse Events (NCI CTCAE v4.0: http://www.jcog.jp/doctor/tool/CTCAEv4J_20150310.pdf).

### 2.14. Auditing (23)

#### 2.14.1. Composition of the coordinating center and trial steering committee {5d}.

The investigators will prepare a written audit plan and based on this, visit the institution to check the approval documents by the head of the institution, review the explanatory and consent documents, and check the contents of the CRFs against medical records. The results of the audit will be submitted to the principal investigator, principal investigator of the institution, and head of the institution.

### 2.15. Ethics and dissemination

#### 2.15.1. Ethics approval and consent to participate (24).

This trial complied with the Declaration of Helsinki and JP Clinical Trial Act.^[18]^ The research ethics committee of Tohoku University approved this trial protocol.

#### 2.15.2. Plans for communicating important protocol amendments to relevant parties (e.g., trial participants, ethical committees) {25}.

If there are changes to the eligibility criteria, outcomes, and analyses, a new version of the protocol will be submitted to the Tohoku University Hospital Ethics Committee for approval.

##### 2.15.2.1. Who will take informed consent? {26a}.

The study administrator or a physician at the collaborating hospital will explain the procedure to the patient or family and obtain their informed consent.

##### 2.15.2.2. Additional consent provisions for collection and use of participant data and biological specimens {26b}.

Not applicable.

#### 2.15.3. Confidentiality {27}.

Participants personal information will be kept confidential in the same way as their medical records in the hospital before, during, and after the trial.

### 2.16. Trial status

The protocol and progress are registered in the University Hospital Medical Information Network (UMIN000023123). Recruitment will begin in January 2022 and is expected to be completed in May 2025.

## 3. Discussion

This study investigated the aspiration pneumonitis prevention of patients with cerebrovascular disorder using practical acupuncture stimulation for the first time. Aspiration pneumonia is primarily caused by subclinical aspiration of nasal, laryngeal, and periodontal secretions that go unnoticed mainly at night. One of the mechanisms by which aspiration occurs is through decreased swallowing and coughing reflexes. The proper functioning of these reflexes requires that substance P synthesized in the cervical ganglion, the sensory branch of the vagus and glossopharyngeal nerves, be maintained at a constant concentration in the peripheral nerves of the pharynx and endotracheal tissue. Substance P is also enhanced by dopamine, which is synthesized in the substantia nigra and striatum. When the deep cortex, including the substantia nigra and striatum, is impaired due to cerebrovascular disease, the ability to synthesize dopamine is also impaired, leading to a decrease in swallowing function.^[9]^ Acupuncture stimulation of the neck improves swallowing function and the expression of 5-HT_1A_ in the arcuate nucleus.^[19]^ Studies that directly investigate the mechanism of dopamine synthesis in the nigrostriatal striatum, as described above, are lacking. However, the use of acupuncture for the treatment of cerebrovascular disease^[20]^ has been shown to improve cerebral blood flow in aged rats and reduce infarct volume.^[21]^ Studies using rats with Parkinson disease, which is a different disease with similar striatum nigra involvement, have shown that acupuncture prevents cell death in the nigra and striatum.^[22]^ The addition of acupuncture to the treatment of patients with Parkinson disease has been reported to significantly increase blood dopamine.^[23]^ From these reports, it can be inferred that acupuncture stimulation may promote dopamine synthesis in the substantia nigra striata as a probable mechanism for improving swallowing function.

In this study, the stimulation will be delivered to the lower limb. This study is based on previous studies showing that stimulation of the lower limbs of patients with cerebrovascular disease improved swallowing function.^[11]^ However, stimulation sites other than the lower limbs have been reported to improve swallowing dysfunction.^[19]^ In the present study, the lower limb was chosen as the stimulus site because of the possibility of continuing stimulation during the 12 months observation period.

The press needles and placebo press needles that will be used in the real stimulation and the control group, respectively are identical in appearances when attached to the skin. Furthermore, there is no difference between the 2 devices in terms of the sensations felt by the participants. Thus, it will be difficult for participants to distinguish between the 2 devices.^[16]^

The same investigator will be responsible for the examination of each patient at different time periods.

All indicators will be assessed by independent assessors.

The principal investigators, statisticians, and outcome assessors will be blinded to treatment assignments until the database is locked.

In conclusion, this study aims to test the therapeutic efficacy and safety of acupuncture stimulation for the prevention of aspiration pneumonia in patients with cerebrovascular disease.

The results of this study will provide evidence-based data, thus opening a new avenue for the use of acupuncture stimulation for aspiration pneumonia prophylaxis in patients with cerebrovascular disease.
